## Abstract

**Background:**

Clinical prediction rules (CPRs) represent well-validated but underutilized evidence-based medicine tools at the point-of-care. To date, an inability to integrate these rules into an electronic health record (EHR) has been a major limitation and we are not aware of a study demonstrating the use of CPR's in an ambulatory EHR setting. The integrated clinical prediction rule (iCPR) trial integrates two CPR's in an EHR and assesses both the usability and the effect on evidence-based practice in the primary care setting.

**Methods:**

A multi-disciplinary design team was assembled to develop a prototype iCPR for validated streptococcal pharyngitis and bacterial pneumonia CPRs. The iCPR tool was built as an active Clinical Decision Support (CDS) tool that can be triggered by user action during typical workflow. Using the EHR CDS toolkit, the iCPR risk score calculator was linked to tailored ordered sets, documentation, and patient instructions. The team subsequently conducted two levels of 'real world' usability testing with eight providers per group. Usability data were used to refine and create a production tool. Participating primary care providers (n = 149) were randomized and intervention providers were trained in the use of the new iCPR tool. Rates of iCPR tool triggering in the intervention and control (simulated) groups are monitored and subsequent use of the various components of the iCPR tool among intervention encounters is also tracked. The primary outcome is the difference in antibiotic prescribing rates (strep and pneumonia iCPR's encounters) and chest x-rays (pneumonia iCPR only) between intervention and control providers.

**Discussion:**

Using iterative usability testing and development paired with provider training, the iCPR CDS tool leverages user-centered design principles to overcome pervasive underutilization of EBM and support evidence-based practice at the point-of-care. The ongoing trial will determine if this collaborative process will lead to higher rates of utilization and EBM guided use of antibiotics and chest x-ray's in primary care.

**Trial Registration:**

ClinicalTrials.gov Identifier NCT01386047

## Background

The benefits of evidence-based medicine (EBM) on the quality of clinical care and improved patient outcomes have not achieved their potential [1]. While numerous EBM guidelines based on high-quality research have been generated and disseminated, data on their uptake into daily clinical practice have often been disappointing due to the challenges of integrating EBM recommendations into the point-of-care [2]. As a result, EBM guidelines often end up as either cluttered paper on the wall of the medical office or idiosyncratic teaching points rarely altering clinical practice. Finding strategies to implement EBM at the point-of-care is critical as monitoring agencies and payers are increasingly using EBM guidelines as markers of quality care.

Clinical prediction rules (CPRs) are a type of EBM that uses validated rules for simple sign or symptom-based probability scores to risk stratify patients for specific prognoses and/or diagnostic assessments [3]. While many high-quality CPRs exist, they have not been regularly implemented for day-to-day care due to inaccessibility at the point-of-care, a problem even more pronounced in the age of electronic health records (EHRs). Our search of the literature found no evidence of attempts to integrate CPRs into EHRs in the ambulatory setting, and only one instance of proposed integration in the inpatient setting [4]. Two well-validated CPRs are the streptococcal pharyngitis (strep throat) and bacterial pneumonia CPRs [5-7]. The strep throat CPR uses five criteria (fever, swollen lymph nodes, tonsillar exudates, strep exposure, and recent cough) to estimate the probability of strep throat in a patient with a sore throat [5]. The pneumonia criteria uses five criteria (fever, tachycardia, crackles, decreased breath sounds, and absence of asthma) to estimate the likelihood of a bacterial pneumonia in the setting of a cough [7]. While both rules have been well-validated in the literature, their use at the point-of-care is suboptimal and new methods for incorporating them into the point-of-care are needed.

Clinical decision support (CDS) systems have been developed as platforms within EHRs to provide evidence at the point-of-care and change physician behavior [8]. In theory, CDS should seamlessly integrate EBM into EHR systems to support the physician in delivering efficient, effective care at the point-of-care, but surprisingly has had equivocal results in ambulatory care [9-13]. Prior attempts at integrating these EBM delivery platforms into EHRs may have been limited by the lack of usability testing of the CDS interface and inadequate provider training prior to use [14]. The lack of usability testing (*i.e.*, useable and usefulness testing) limits the ability to assess if CDS can be effectively integrated into clinical workflow (usable) or is something desired by the clinician (usefulness). This often forces clinicians to either alter their workflow or work around the CDS tool. The lack of provider training in assessing the usability and usefulness of CDS tools and therefore how to best incorporate these tools into workflow has also limited their penetration into clinical practice. As a platform for building EBM into EHRs, CDS could significantly improve clinical workflow and quality delivery by providing access to many well-validated frontline decision aids like CPRs that are currently underutilized.

We have developed an integrated clinical prediction rules (iCPR) clinical decision support program that incorporates two well-validated CPRs (Walsh CPR for Streptococcal Pharyngitis and the Heckerling CPR for Pneumonia) into an outpatient EHR system used by the providers of nearly 40% of the nation's patients. This article discusses the design, development, usability testing, training, and implementation of study.

## Methods/Design

The iCPR study was designed to test the feasibility and effectiveness of incorporating the strep throat and pneumonia CPRs into the EHR in a primary care practice. The two main aims supporting this goal were to assess adoption of the iCPR program in primary care and to assess the impact of the iCPR

### Prototype development

Over a period of three months, an interdisciplinary team designed the first prototype iCPR. This team included expertise in CPRs, primary care, usability, clinical informatics, and a deep knowledge of the capabilities and limitations of CDS in the commercial EHR. Early in the prototype design process, several major design issues were considered. Figure 1 displays the basic conceptual model of the iCPR tool.

**Figure 1 F1:**
[figure not shown]
**iCPR conceptual model**.

### Technical Considerations

#### Assessment Tool

We considered several options within the EHR to house the iCPR assessment tool based on discussions with the vendor, provider familiarity with the vendor's CDS tools, and provider workflow. The EHR vendor initially suggested using a 'smart' form for iCPR because it has enhanced visual aesthetics and expedites calculations. However, providers had almost no daily experience with this form in the practice under study and, more importantly, would have required more manual input by providers to complete the full iCPR workflow. As a result, the team selected to use dynamic flowsheets for calculations that were relatively unknown and had some formatting limitations, but minimized 'clicks' and manual data entry.

#### Restriction of alerts

iCPR is a practice-based randomized clinical trial that had to be seamlessly integrated into workflow without disrupting control providers. To achieve this, iCPR was designed to activate only for providers randomized to the intervention. Furthermore, the tool is further restricted to the providers' outpatient primary care EHR interface, because they may be practicing in other clinical settings with the same EHR but potentially vastly different workflows.

#### Alerts, overrides and triggers

Alerts are an active research area in the CDS literature. They can be categorized on two spectrums of activity: active versus passive and mandatory versus optional. A major early design consideration was the whether to use active (interrupting) or passive (non-interrupting) alerts [15,16]. In the context of our commercial EHR, active alerts 'pop-up' at the user, directly interrupting their workflow in order to draw their attention. Passive alerts are non-interrupting, minimally intrusive alerts, and would use non-interrupting flags or highlights to draw the CDS alert. Mandatory alerts require the user to take the designated action or explain the reason for overriding the CDS, while optional alerts allow the user to ignore the CDS alert without an explanation. Prior literature has demonstrated the superior efficacy of active mandatory alerts; however they are more disruptive to workflow, which contributes to the low uptake of CDS tools [10]. Their use is also problematic in the increasingly crowded CDS dashboards populating the primary care EHR. Balancing these factors, the development team selected a two-step system in which an early-in-workflow passive mandatory alert and a later-in-workflow active mandatory alert were combined. Mandatory alerts were chosen for both because data on reasons for declining the CDS tool were critical to iterative improvements.

Another major design issue was the choice of where in the primary care workflow the alert should launch and what the specific trigger diagnoses or orders should be. The pros and cons of various workflow triggers options were discussed and consensus was achieved for the initial prototype. The agreed trigger points for the tool were one of three workflow locations: chief complaint, relevant and specific encounter diagnoses, or a less specific encounter diagnosis in combination with a relevant antibiotic order (Table 1 lists the relevant trigger diagnoses and orders). The early-in-workflow passive mandatory alert triggered from the chief complaint, while the later-in-workflow active mandatory alert triggered from diagnosis and/or orders to ensure users did not simply forget to use the CDS tool.

**Table 1 T1:** Chief complaint, diagnosis, and diagnosis/antibiotic combination triggers of iCPR tools

Strep	Pneumonia

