#### Provider eligibility, consent, and randomization

All primary care providers within the medical practice were eligible for the study. The practice includes 149 primary care faculty, residents, and nurse practitioners divided into four units on the same floor. The study design was a randomized control trial in which the providers within the academic medical center outpatient practice were the unit of randomization. Faculty providers were randomized via random number generator to intervention or control in a 1:1 ratio. Medical residents were randomized within blocks according to their outpatient ambulatory care month (a period with substantially increased outpatient clinical activity) assignments to ensure even distribution throughout the academic calendar. However, due to changes in the resident calendar in year two of the study, any additional medical resident providers entering the system were added in a 1:1 fashion. Only providers randomized to the intervention are triggered by the EHR to use the iCPR tools. After randomization, all providers were invited to standardized educational forums for consent and training (if randomized to the intervention).

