### Follow-up

#### Process

The process measurement battery is designed to assess the uptake of the iCPR tool by providers and to document the utilization of each part of the tool. This is a critical outcome because poor provider utilization of CDS and other EBM and quality improvement tools has been a frequent barrier to their success [9]. Measured markers of utilization (see Table 2) include rate of accepting the iCPR tool when triggered in an encounter, using the relevant iCPR risk calculator, use of the bundled order set linked to each risk calculator score, and use of each section of the bundled order set (orders, documentation, patient instructions, *et al*.). The rate of triggering of the iCPR tool from the various sections of the EHR will be measured in the intervention and control arm. The control arm is measured through 'shadow' simulation of the iCPR tool in the control patients, which allows comparison of triggering rates in the control and intervention.

**Table 2 T2:** Outcome measures

CPR	Process Outcomes	Primary Outcome	Secondary Outcomes
Pneumonia	% of eligible encounters accepting iCPR and using bundled order set	Number of antibiotics prescribed	Number of chest x-ray ordered
Strep throat	% of eligible encounters accepting iCPR and using bundled order set	Number of antibiotics prescribed	Number of rapid strep tests and throat cultures ordered

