#### Outcome

The outcome measurement battery is designed to detect changes in clinical practice that are most likely to result from use of the iCPRs. The primary outcome is the difference in antibiotic prescribing frequency among patient encounters eligible for the iCPR tool among intervention compared to control providers. For example, for all patients presenting with symptoms that launch the pneumonia or strep throat tools, data will be collected from the EHR on the number of prescriptions for antibiotics written by providers randomized to the iCPR compared to usual-care arms, respectively. We will also examine the rate of chest x-ray orders and rapid strep throat test orders between intervention and control providers as a secondary outcome (see Table 2).

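### The primary-outcome denominator depends partly on diagnosis labels entered after randomisation, and only intervention providers are interrupted for entering them, so the arms' prescribing rates can diverge without any change in prescribing

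*Protocol article*

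**What the plan says.** All places are in the protocol article.

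- **Randomisation comes first.** Under Provider eligibility, consent, and randomization, "providers within the academic medical center outpatient practice were the unit of randomization". Intervention providers are then trained on the tool.
- **Only one arm is alerted.** The same section states: "Only providers randomized to the intervention are triggered by the EHR to use the iCPR tools". Restriction of alerts says the same.
- **Eligibility is by trigger alone.** Patient inclusion and exclusion criteria sets no patient-level criteria. Alerts, overrides and triggers gives three routes: chief complaint, a specific diagnosis, or a less specific diagnosis combined with an antibiotic order.
- **The alerts differ by route.** The chief-complaint alert is early and passive. For the other routes, "the later-in-workflow active mandatory alert triggered from diagnosis and/or orders to ensure users did not simply forget to use the CDS tool". Active means a pop-up that interrupts; mandatory means the provider must act or give a reason for overriding.
- **Controls are counted silently.** Process describes a shadow "simulation of the iCPR tool in the control patients, which allows comparison of triggering rates in the control and intervention".
- **The outcome is conditional on eligibility.** Under Outcome, antibiotic prescriptions are counted "for all patients presenting with symptoms that launch the pneumonia or strep throat tools".
- **The model is fixed.** Statistical Analysis specifies a GEE clustered on clinician with intervention group as the only explanatory variable. It also compares triggering between arms, overall and by trigger location.

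**The concern.** The provider's own coding helps decide whether an encounter is analysed. That coding happens after allocation, by people who know their arm from the training and the pop-ups, and the cost of choosing a trigger diagnosis differs by arm. This is the setting for post-randomisation identification bias: the two denominators may stop being comparable although the providers were randomised.

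The protocol recognises the pressure itself. Alerts, overrides and triggers concedes that active mandatory alerts disrupt workflow more, and the Background notes that ill-fitting decision support leads clinicians to work around it. Usability testing may weaken that pressure but does not remove it.

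At stake is the reading of the primary comparison. A tool that truly reduces prescribing could look weaker or ineffective.

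**Working it through.** **1. The route through Table 1.** Compare the same pneumonia-type visit under two labels:

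| Label entered | No antibiotic | Antibiotic ordered |
|---|---|---|
| *Bronchitis* (stand-alone trigger) | counted, pop-up | counted, pop-up |
| *Cough* (combination trigger) | not counted, no pop-up | counted, pop-up |

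Changing the label avoids the pop-up only when no antibiotic is ordered, and exactly that visit leaves the denominator. The numerator is untouched, so the rate rises.

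**2. Which tool is exposed.** *Cough* and *URI* stand only in the pneumonia column of the combination list. The pneumonia chief-complaint list has no plain cough, and Patient inclusion and exclusion criteria names a bronchitis diagnosis as that tool's common trigger. For strep, *Sore throat* is a chief-complaint trigger, so many such visits should be secured before a diagnosis is coded. Strep is less exposed, not immune: its combination list holds labels such as *Painful swallowing*, close to the stand-alone *Odynophagia*.

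**3. The plan's own figure.** Power Calculation gives 535 encounters per condition, 30% baseline, a 12% reduction, 5% significance, 80% power and an intraclass correlation below 0.15. Reading the reduction as 30% to 18%, a two-sided test needs 198 per arm (396 in total), or 214 per arm (428) with continuity correction. With 149 providers and an assumed correlation of 0.10:

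428 × (1 − 0.10) / (1 − 428 × 0.10 / 149) = 385.2 / 0.713 = 540, close to 535.

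The sample size is not in dispute; the 30% and 18% carry forward.

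**4. Size of the shift, no true effect.** Take 100 trigger-labelled encounters, 30 with an antibiotic, none initially entering by the combination route. Let b be the assumed share of the 70 non-antibiotic encounters lost from the intervention arm. Rate = 30 / [30 + 70(1 − b)].

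- b = 10%: 30/93 = 32.3% (+2.3 points), triggers down 7%
- b = 20%: 30/86 = 34.9% (+4.9), triggers down 14%
- b = 30%: 30/79 = 38.0% (+8.0), triggers down 21%

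If a share c is already secured by chief complaint and a share r of the rest is relabelled, b = r(1 − c). With r = 20%, c = 0, 50% or 100% gives b = 20%, 10% or 0, and rates of 34.9%, 32.3% or 30.0%. The documents give neither r nor c.

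**5. Cost to a real effect.** Suppose the true rates are 30% and 18%, with 198 effective encounters per arm held fixed. The observed intervention rate is 18 / [18 + 82(1 − b)]: 19.6%, 21.5% and 23.9% for b = 10%, 20% and 30%. With d the difference from 30% and SE = √{[0.30 × 0.70 + p(1 − p)]/198}, power = Φ(d/SE − 1.96). It falls from 81% to 67%, 49% and 28%.

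**6. Other patterns.** Leaving Table 1 altogether could remove visits of either kind. Losing 10%, 20% or 30% of the antibiotic visits instead gives 27/97 = 27.8%, 24/94 = 25.5% or 21/91 = 23.1%, with triggers down only 3%, 6% or 9%. An equal 20% loss of both kinds gives 24/80 = 30.0%, no bias.

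**The case against.** The strongest replies are these.

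- **Relabelling is only a possibility.** No passage reports it, and giving an override reason is an available alternative. The pop-up fires once the label is entered, so avoidance must be learned or come from changing the code. The document does not say whether a recoded visit stays counted. This stands: the claim is that the denominators can diverge, not that they will.
- **Monitoring exists.** Triggering is compared by location, weekly reports track the diagnostic triggers, and chart reviews check whether triggering was appropriate. This would probably expose a large shift in the diagnosis route. It does not correct one, and a loss of antibiotic visits barely moves the total count.
- **Sensitivity analyses belong in an analysis plan that is not shown.** Their absence from a condensed article is no fault. The point rests on what the article does fix: the eligibility rule, the conditional denominator and the model.

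A reader might infer that the bias would persist even if the antibiotic-combination encounters were handled correctly. The documents do not support that. The selective loss of non-antibiotic visits depends on the combination route keeping the antibiotic ones. Without that route, bias needs relabelling that differs by antibiotic status, or labels outside Table 1. Nor does the within-table mechanism manufacture a false reduction; it works against the intervention.

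**Conclusion.** The concern holds in this limited form. Eligibility depends partly on labels entered after randomisation, under an incentive that exists in one arm only. For the pneumonia tool chiefly, within-table relabelling would inflate the intervention rate and could hide a true reduction. Relabelling outside the table could bias either way. An assumed 10% to 30% loss of non-antibiotic visits moves a 30% rate by 2.3 to 8.0 points, against a planned 12-point fall. These are illustrations: the loss is assumed, and chief-complaint capture would reduce it by an unknown amount. GEE with an exchangeable structure handles clustering, not selection into the denominator. The point merits a change to the analysis; it does not show that the trial's result is biased.

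**What to change.** 1. Apply one identical query in both arms that counts every encounter with any Table 1 chief complaint or diagnosis, whether or not an antibiotic was ordered. Where the log allows, count an intervention encounter if a trigger label was ever entered, even if later changed. A query of final labels alone would not do, because those are what relabelling alters.
2. Report the antibiotic comparison on this denominator, separately for strep and pneumonia.
3. Add a sensitivity analysis restricted to chief-complaint-triggered encounters, which are identified before the interrupting alert.
4. State in advance that if triggering rates differ by arm, or if these analyses disagree with the primary result, neither a difference nor its absence will be attributed to the tool.

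**Cost.** All data already come from the EHR and a shadow query exists, so this needs extra programming and two further analyses, with no change to care. The all-Table-1 set takes in less relevant visits and dilutes the effect. The chief-complaint set is smaller and less precise, especially for pneumonia, and its alert, though passive, is also mandatory, so it is not wholly free of incentive. Neither set recovers every visit moved outside Table 1, which is why the limit on attribution is needed.

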**Chief Complaint**	
Sore throat	Possible pneumonia
Strep pharyngitis	Pleurisy
Dysphagia	Chest hurts when breathing
Throat hurts	Productive cough with shortness of breath
Throat discomfort	New onset shortness of breath
Recent contact (children) with pharyngitis	
**Diagnosis**	
Acute pharyngitis	Acute bronchitis
Bacterial pharyngitis	Acute bronchitis with bronchospasm
Chronic pharyngitis	Aspiration pneumonia
Difficulty in swallowing	Atypical pneumonia
Odynophagia	Bronchiectasis with acute exacerbation
Pain on swallowing	Bronchitis
Pharyngitis	Bronchitis with chronic airway obstruction
Pharyngitis acute	Bronchitis, chronic
Pharyngitis due to group A beta hemolytic Streptococci	Bronchitis, not specified as acute or chronic
Sore throat	CAP (community acquired pneumonia)
Sore throat (viral)	Community acquired pneumonia
Sore throat - chronic	Legionella infection
Sorethroat	LRTI (lower respiratory tract infection)
Strep sore throat	Pneumonia
Strep throat	Pneumonia, aspiration
Streptococcal pharyngitis	Pneumonia, community acquired
Streptococcal sore throat	Pneumonia, organism unspecified
Throat discomfort	Productive cough
Throat infection - pharyngitis	Sputum production
Throat pain	
Throat soreness	
Viral pharyngitis	
